## Abstract

**Background:**

Treatment of locally advanced oesophago-gastric adenocarcinoma usually entails neo-adjuvant chemotherapy (NAC) and surgery. Surgery is associated with high morbidity and mortality. Cardiopulmonary reserve of patients having major surgery is related to postoperative outcomes. Complications are associated with poorer quality of life and may affect prognosis. Preventing complications may be beneficial to both of these and have cost implications. Prehabilitation may improve recovery from surgery by increasing a patients’ fitness before surgery. Designing a potentially cost and resource effective regimen which improves cardiopulmonary reserve may have a beneficial impact on patient outcomes after surgery.

**Methods:**

The ChemoFit study is a non-randomised, single-arm and single-centre pilot study designed to investigate the feasibility of a home-based prehabilitation exercise intervention for patients receiving neoadjuvant treatment prior to oesophago-gastric surgery. Forty patients will be recruited at a single high-volume centre. The simple, home-based exercise intervention involves patients increasing their daily step-count during and after NAC and in the weeks leading up to surgical resection of the cancer. Additionally, quality of life assessments (QLQ-C30 and QLQ-OG25), oncological treatment delivery and participant perceptions of the study assessed by focus groups and questionnaires will be performed. The primary outcomes are to assess feasibility of the exercise intervention. The secondary outcomes will evaluate changes in cardiopulmonary reserve, sarcopenia and fat composition.

**Discussion:**

It is anticipated that during an important teachable moment, the diagnosis and treatment of cancer, our patients will be open to the possibility of improving their fitness during chemotherapy and before major cancer surgery. It is possible that the negative impact of NAC on cardiopulmonary fitness could be prevented by implementing a home-based prehabilitation programme during and after NAC, prior to surgery for oesophago-gastric adenocarcinoma.

**Trial registration:**

This study has been approved by the Health Research Authority (REC 18/WA/0427). Newcastle upon Tyne Hospitals NHS Foundation Trust (NUTH) will act as the study sponsor and the work is funded by a grant awarded by The Jon Moulton Charitable Foundation, supported by a research post funded by the Sir Bobby Robson Foundation. Trial registration: Clinicaltrials.gov, NCT04194463. Registered 11th December 2019—retrospectively registered, https://clinicaltrials.gov/ct2/show/NCT04194463.

## Introduction

Curative treatment of locally advanced oesophago-gastric adenocarcinoma usually entails neo-adjuvant chemotherapy (NAC) followed by surgery and then postoperative adjuvant chemotherapy. Multimodal therapy has been shown to be superior to surgery alone [1, 2]. This type of major surgery is unfortunately associated with high morbidity and mortality [3, 4]. It has been shown that cardiopulmonary fitness prior to major surgery is related to postoperative outcomes [5]. Previous work has demonstrated a significant and sustained reduction in fitness during NAC given for oesophago-gastric cancer, which not only affects daily activities and quality of life, but also decreases the physical reserve of the patient before they undergo major surgery [6, 7]. Both a reduction in objective cardiopulmonary reserve, measured by cardiopulmonary exercise testing (CPET), and reduction in muscle mass (sarcopenia) on CT scan analysis in the interval between commencing chemotherapy and undergoing surgery has previously been observed [7]. Complications of major surgery are associated with poorer quality of life in the short-term and worse prognosis [8]. Further, they can delay or prevent the administration of post-operative chemotherapy, which may impact on disease recurrence. Preventing these complications may improve surgical outcomes, patient health and survival from oesophago-gastric cancer. In addition, exercise may have beneficial effects on improving immune surveillance and reducing inflammation; reversing abnormalities that may be associated with tumour recurrence and growth [9].

High-intensity exercise interventions have already demonstrated the ability to prevent the decline in health observed in other patient groups undergoing chemotherapy [10, 11]. These programmes require a large financial investment, time commitment and the use of complex hospital resources. In a wide geographical area, attending hospital-based interventions can be challenging to implement, particularly when patients are unable to travel due to the impact of their treatment, and the cost of travelling long distances. To help overcome these barriers, we have developed a home-based exercise intervention, which could be utilised by a large number of patients at any one time. The aim of the pilot study is to assess the feasibility, acceptability and safety of this intervention on a small group of patients. Further, the impact of such a regimen on cardiorespiratory fitness and sarcopenia will be assessed and its effect on biomarkers measuring immune function and frailty explored. It is hoped that the data from this study will help to inform future randomised studies into the benefit of exercise programmes.

## Methods

### Study design

This is a prospective, single-group, single-centre pilot study investigating the feasibility and acceptability of a home-based exercise intervention during oncological treatment of patients presenting with operable advanced adenocarcinoma of oesophagus, gastro-oesophageal junction and stomach. Patients will be invited to participate in the study which involves provision of a home-based exercise intervention before, during and after NAC, and in the weeks leading up to surgical resection of the cancer.

### Study aims

The primary aim of the pilot study is to assess the feasibility of the home-based exercise intervention. This will be assessed by the measurement of the recruitment rate, completion rate and individual compliance with the intervention (i.e. do patients perform the exercise, engage with telephone support and record their activity levels in accordance with protocol).

The secondary aim of this study involves the preliminary assessment of benefit to patients’ physiology and quality of life related to the exercise intervention. Results will be used to inform the design of a larger scale randomised controlled trial evaluating the impact of an exercise regimen on patients’ cardiopulmonary fitness, sarcopenia, quality of life and potentially postoperative outcomes such as morbidity and length of hospital stay. The ChemoFit study (as a part of the secondary outcomes) will aim to assess cardiopulmonary fitness as measured using cardiopulmonary exercise testing (CPET), changes in muscle mass (sarcopenia) as measured using computed tomography (CT), handgrip strength and quality of life utilising QLQ-C30 and QLQ-OG25 questionnaires [12, 13]. Patient’s physical activity will be measured by daily step counts using waist-worn pedometers, which serve as the method of quantifying activity levels and will help with prescribing home-based activity increases. The oncology treatment will be assessed by recording chemotherapy dose reduction and delays, percentage of planned chemotherapy delivered and admissions to hospital with chemotherapy induced toxicity. Acceptability of the intervention will be assessed with patients taking part in the study by eliciting their views and experiences via focus group discussions. The qualitative component of this feasibility study will obtain participants’ views and experiences of the intervention via focus groups, including what they perceive to be barriers and facilitators to using it in order to assess acceptability. The purpose of this qualitative component is to inform the design of future studies and there is no plan to include acceptability or any other qualitative work in future designs. Up to five focus group discussions will be conducted by a researcher using a topic guide containing questions designed to address the objectives of the study.

It is not intended to use any data obtained from the ChemoFit study in future randomised controlled trials.

### Inclusion and exclusion criteria

Patients with locally advanced adenocarcinoma (T3+, T1/2 N+) [14] of the oesophagus, oesophago-gastric junction or stomach and a planned NAC regimen including the locally used ECX, ECX variant [1] or FLOT [15] regimens will be eligible to participate in the study. Participants 18 years of age or older and able to consent to the study and carry out the planned intervention and CPET tests required in the protocol will be invited to participate.

Exclusion criteria are patients treated with neo-adjuvant radiotherapy or chemoradiotherapy, patients in whom CPET is contraindicated [16], and patients with inoperable tumours.

### Patient selection and consent process

Patients will be identified during the multidisciplinary cancer staging process at the Northern Oesophago-gastric Unit. Suitable patients, who meet the eligibility criteria, will be provided with a patient information sheet (PIS) explaining the study. They will be consented for the study after the finalised oncological treatment plan has been agreed by the multidisciplinary team and discussed with the patient. By providing a PIS early in the staging process patients will have sufficient time to consider their participation in the study and ask questions. All eligible patients will be approached, and participation will be voluntary: they will be able to withdraw consent at any point during the study. Patients who have not agreed to take part in the study by the time they start their first chemotherapy session will not be eligible to participate.

During the first study enrolment meeting, informed, written consent will be obtained prior to any study procedures and each patient will be asked to complete baseline QLQ-C30 and QLQ-OG25 quality of life questionnaires [12, 13]. The handgrip strength of their dominant hand will be measured using grip strength dynamometer (T.K.K. 5101 GRIP-D, Takei scientific instruments Co., Ltd., Japan). Participants will be provided with a simple, easy to use pedometer (Walking style One 2.1, Omron Healthcare UK Ltd., UK), resistance band (BodyMax resistance tube, BodyMax Ltd., UK) and exercise diaries. They will receive information about what the exercise intervention involves and taught how to use the pedometer, resistance band and exercise diaries.

### Intervention

#### Baseline measurement

Once enrolled into the study, participants will immediately enter a 1-week period of monitoring using a pedometer to record their habitual physical activity (daily step count). This initial period will be used to establish a baseline physical activity level for each participant and will be used to calculate each individual’s median daily step count. Baseline CPET and CT data will be collated at this point. Both CPET and CT data will have been performed as part of routine clinical care during the multidisciplinary team (MDT) staging process (Fig. 1).

**Fig. 1 Fig1:**
[figure not shown]
Consort diagram of the study

#### The exercise intervention

The exercise intervention will start immediately following completion of the 1-week period of baseline monitoring. The intervention will continue during chemotherapy and afterwards in the time period between the end of chemotherapy and the planned surgical resection. The intervention will be personalised to each patient based on their baseline level of activity (as recorded by a pedometer during the first week of observation), age, general health, motivation, and social circumstances with the aim of achieving the greatest improvement in their cardiopulmonary fitness.

The exercise intervention will aim to achieve an increase in daily step count of 2000 steps per day, 7 days per week [17]. This increase in physical activity (step count) will be achieved by walking or jogging at moderate intensity for a target of 30 min per day, each day (this is one ‘bout‘ of moderate intensity exercise) [18]. Participants will be instructed on how to achieve moderate intensity physical activity using the modified Borg rating of perceived exertion (RPE) scale (0–10) aiming to achieve an RPE level between 3 and 4 (moderate to somewhat strong exertion) [19]. This will ensure that the intensity at which these 30-minute bouts of physical activity are maintained throughout the entire exercise period. Patients will be asked to record their daily step count at the end of every day and the RPE for the 30-min bout of exercise. The Borg scale will be used as a tool to describe levels of home-based physical activity throughout the study.

After the first week of the intervention, patients will be contacted by a member of the research team; and with the research team’s support they will be given the option to maintain or to increase their step count further if they feel that they have managed to achieve the prescribed amount of steps in the previous week. The same approach will be used after each week of the intervention. The aim of this is to facilitate a participant-led increase in daily physical activity based upon increasing the daily step target. Participants will also be encouraged to perform other physical activities like jogging, swimming, cycling or group activities if they wish and feel able to do so.

The participants’ progress will be monitored in a daily diary entry.

After completion of NAC, a further enhanced increase in the daily activity above the current physical activity level will be implemented providing the patient is comfortable with this progression. The level of this increase will be based on current progress and, as such will be tailored to individual needs and circumstances. This incremental period will start 7 days after the last Capecitabine tablet (given as part of the chemotherapy) and continue until the end of the study and the last study visit.

#### Strengthening exercises

Strengthening exercises will be performed alongside the exercise intervention. Strengthening exercises will be performed every day, 7 days per week, and will start after the end of the baseline observation week has been completed. The patients will be taught how to perform two sets of five simple exercises (sit to stand/wall squat, biceps curl, upright row, leg abduction, wall press), each for 1-min duration by a member of the research team. This equates to 10 min of strengthening exercise in total each day. Exercises have been selected to strengthen major body muscle groups. Each exercise will be prescribed at two levels of intensity in order to tailor them to individual fitness levels. A booklet demonstrating the correct performance of the strengthening exercises will be given to each patient to take home. They will receive weekly telephone calls to encourage and reinforce the importance and conduct of these strengthening exercises.

#### Interim analysis of step-based regimen

Once the first 10 participants have each completed the first week of the exercise regimen during NAC, we will perform an interim analysis of their achieved daily step count during this first week. If ≥ 60% of participants have not achieved the prescribed daily step count for at least 5 days of this week, then we will lower the increment in steps described within the protocol. We will change this initial increment to 1000 steps above baseline daily step count for all participants recruited after the interim analysis.

Conversely, if ≥ 80% of participants have achieved the prescribed daily step count for all 7 days of the first NAC exercise week, we will increase our first increment to 3000 steps above baseline daily step count for all participants recruited after the interim analysis.

This strategy has been chosen to ‘fine adjust’ our initial step increment after the first observation week as it is difficult to predict how demanding this increment is going to be for patients, especially in the context of starting chemotherapy treatment. There is no current evidence to guide this decision. Based on the findings from the Active-at-Home HF pilot study in stable chronic heart failure patients, we replicated the same physical activity steps/day in our patients, i.e. an increase of 2000 steps/day from baseline physical activity [17].

#### Weekly telephone reporting, reinforcement and encouragement

A member of the research team will contact each study participant once per week by telephone in order to provide support, reinforce the aims of programme and reiterate the benefits, monitor activities and exercises, collect the previous week’s data and provide positive feedback. Participants will be encouraged to reflect upon the previous weeks achievements and discuss any problems or factors which may have inhibited progress with a view to identifying strategies to overcome these problems, where possible. These will be recorded by the research team. Patients will be given the opportunity to increase their daily target for the next week if they feel that this is achievable or appropriate.

#### Completion of the exercise intervention

The end of the study period is defined as the last full week of exercise before surgery. Participants will complete an end of study CPET, hand grip strength measurement, blood sampling and quality of life questionnaires during the 2 weeks prior to their scheduled surgery. A CT scan, which is performed as part of routine clinical care prior to the surgery, will be used for comparison with the initial CT scan to measure sarcopenia.

#### Cardiopulmonary exercise testing

The end of study CPET will be performed in accordance with the American Thoracic Society/American College of Chest Physicians guidelines [20]. Patients will perform a symptom-limited continuous ramped test on cycle ergometer (Ergoselect 200, Ergoline GmbH, Germany). Metabolic gas analysis will be conducted via the metabolic cart (Ultima Series, MGC Diagnostics, USA). CPET data will be analysed using the Breeze SuiteTM software (Ultima Series, MGC Diagnostics, USA). This will be performed initially alongside staging investigations, which is part of normal routine clinical care and additionally prior to surgery as part of the study protocol.

#### Usual clinical care during the study

All participants enrolled in the study will be managed according to the standardised patient pathway that already exists. Patients are reviewed by the surgical team and counselled with regard to the treatment options that are available. Those patients that are struggling nutritionally are then reviewed by one of two specialist upper gastrointestinal dietitians. If patients are unable to manage sufficient calorie input without assistance, they may have a naso-enteric feeding tube placed or a feeding jejunostomy so that they receive sufficient calories.

### Study outcomes

The primary and secondary outcomes are defined in Table 1 and Table 2.

**Table 1 Tab1:** The primary outcomes of the study

Primary outcome measures	Definition	Success threshold
Recruitment rate	Proportion of all patients approached who meet the eligibility criteria and agree to enter the study	*50%*
Completion rate	Proportion of all patients that enter the study that remain participants at the end of the defined study period	*75%*
Compliance	Percentage of intervention days when the patient was wearing his/her pedometer, was contactable every week and was recording his/her daily step count	*75%*

**Table 2 Tab2:** The secondary outcomes of the study

Secondary outcome measures	
CPET	Change in VO2 peak (ml/min/kg), change in VO2 at AT (ml/min/kg) and change in FEV1 prior and post intervention
Sarcopenia	Change in amount of L3 level skeletal muscle area determined on CT scan by methodology described by Perthen et al. [21], change in fat composition and volume measured by CT scan and change in grip strength pre and post intervention
Exercise intervention	Change of step count throughout the intervention
Oncological treatment	Number of patients with dose reductions or who terminate chemotherapy early, percentage of planned chemotherapy delivered, admissions to hospital with chemotherapy induced toxicity
Quality of life	Change of score on validated quality of life questionnaires QLQ-C30 and QLQ-OG25 pre and post intervention
Acceptability	Qualitative evidence generated from focus group discussions with participants

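### The Table 1 definition of compliance omits exercise performance, which the study aims include, and gives no rule for scoring weekly contact within a percentage of days

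*Protocol article*

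**What the plan says.** The Study aims section of the protocol article says that feasibility, the primary aim, is assessed by recruitment, completion and individual compliance with the intervention. It explains compliance as: "do patients perform the exercise, engage with telephone support and record their activity levels in accordance with protocol". That is three elements, with exercise first.

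Table 1 (Study outcomes) gives the operational definition, with a threshold of 75%: "Percentage of intervention days when the patient was wearing his/her pedometer, was contactable every week and was recording his/her daily step count". The completion rate, also with a threshold of 75%, is: "Proportion of all patients that enter the study that remain participants at the end of the defined study period". The recruitment rate, with a threshold of 50%, counts eligible patients who agree to enter.

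The intervention has two daily parts. On walking: "The exercise intervention will aim to achieve an increase in daily step count of 2000 steps per day, 7 days per week". On strength work: "Strengthening exercises will be performed every day, 7 days per week". On daily records: "Patients will be asked to record their daily step count at the end of every day and the RPE for the 30-min bout of exercise". On telephone support: "A member of the research team will contact each study participant once per week by telephone".

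Table 2 lists change of step count during the intervention as a secondary outcome, with no threshold. Whether the prescribed steps are reached is assessed in one place, the interim analysis, which covers the first 10 participants in their first exercise week and decides the starting increment for later recruits. The Statistical analysis section says that the primary outcomes are only described.

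**The concern.** The two definitions of the same primary outcome differ on its central element. The aims ask whether patients do the exercise. Table 1 asks whether they can be monitored: pedometer worn, steps written down, patient reachable. Neither the step target nor the strengthening exercises enter any outcome that has a success threshold. A result above 75% could be reported as compliance with the intervention and carried into the design of the planned randomised trial, when it shows only that patients cooperate with monitoring.

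The second problem is one of units. Table 1 counts days, but contact takes place weekly, and no rule connects the two. The score, and which side of 75% it falls on, can then depend on a choice that the article does not state.

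**Working it through.** No formula underlies the 75% threshold, so there is no planned figure to reproduce. The check compares the two definitions and then scores hypothetical patients by counting days.

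**Element by element**

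| Element | Study aims | Table 1 compliance |
|---|---|---|
| Exercise performed | yes | absent |
| Telephone support | yes | yes, as weekly contactability |
| Activity recorded | yes | yes, as daily step count |
| Pedometer worn | not named | yes |

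**Step 1: a patient who does no added exercise.** The length of the intervention is not stated; assume 16 weeks, or 16 × 7 = 112 days. The patient wears the pedometer and records every day, answers all 16 calls, never exceeds baseline steps and does no strengthening.

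- Table 1 compliance: 112/112 = 100%, above 75%.
- Days meeting the step target: 0/112 = 0%.

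The assumed length does not affect either result. The same patient also counts as recruited and as a completer, so all three primary thresholds can be met without any increase in activity.

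**Step 2: the weekly condition.** Take a patient with full wearing and recording who misses m of W weekly calls. Four readings are possible:

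- (a) Each week's contact status applies to its 7 days: 7(W − m)/(7W).
- (b) No day counts unless every week was contacted: 0 if m ≥ 1.
- (c) Mean of the three components: [1 + 1 + (W − m)/W]/3.
- (d) Contact is ignored: 1.

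With one missed call and assumed lengths of 12, 16 and 20 weeks:

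- (a) 11/12 = 91.7%, 15/16 = 93.8%, 19/20 = 95.0%.
- (b) 0% at each length.
- (c) 97.2%, 97.9%, 98.3%.
- (d) 100%.

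With 5 missed calls over 16 weeks:

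- (a) 77/112 = 68.8%, below 75%.
- (b) 0%, below 75%.
- (c) (1 + 1 + 11/16)/3 = 89.6%, above 75%.
- (d) 100%, above 75%.

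After one missed call, only reading (b) gives a score below 75%. Reading (a) falls below the threshold once more than a quarter of calls are missed: 4 of 16 gives exactly 84/112 = 75%.

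**The case against.** The strongest reply is that the plan does look at exercise. Table 2 includes change of step count, the interim analysis checks whether prescribed steps were reached, diaries record daily steps and exertion, and the weekly calls monitor activity. The patient in step 1 would show up in the step-count outcome. The primary outcomes are descriptive, so no formal test depends on the figure. This stands against the inference that the study cannot tell whether patients exercised: the documents do not support that. It does not remove the mismatch, because the aims place exercise within a primary outcome and Table 1 takes it out.

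A reader might also infer that the weekly condition cannot be scored by day, or that most patients must fail it. Neither follows. Reading (a) is a workable daily rule. At 95% success per call, the chance of reaching a patient every week would be 0.95^12 = 54% over 12 weeks and 0.95^20 = 36% over 20. These figures matter only under reading (b), and they also assume the duration, the success rate, independence between calls, and that one failed call makes a patient uncontactable. The documents state none of these. The full protocol may hold a scoring rule, so this part is a request to state one.

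Two cautions about a remedy also stand. Targets are participant-led and may rise weekly, so scoring against the current target would mark down a patient who chooses a higher one. The interim criterion of at least 5 days in the week is a first-week group rule for setting the increment. It is not a compliance threshold for the whole period.

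**Conclusion.** The point holds in a limited form. The article defines one primary outcome in two ways, and the version with the threshold leaves out exercise performance. Compliance of 100% is compatible with no increase in activity, whatever the length of the intervention. Exercise performance is left to a secondary outcome without a threshold.

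The weekly condition is ambiguous but can be scored. The range from 0% to 100% for one patient rests on an assumed 16 weeks and 5 missed calls, and shows only that the rule needs to be stated. The documents give no basis for estimating how many of the 40 participants would be affected by either problem. Because this is a primary outcome intended to inform a later trial, the two definitions should be reconciled.

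**What to change.** Replace the single composite with separately reported measures:

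1. **Monitoring adherence:** days with the pedometer worn and the step count recorded, divided by intervention days. The 75% threshold can stay here.
2. **Telephone contact:** calls completed divided by calls scheduled.
3. **Compliance, matching the study aims:** days on which the step target was met, divided by all intervention days, with unrecorded days counted as not met. Calculate it per patient, then summarise. Use a fixed reference, namely each participant's baseline plus the initial increment assigned to that participant, so that raising one's own target carries no penalty. Report results against the target in force each week as a supplement.
4. **Strengthening adherence:** report only if the diary or weekly call captures it. The article does not describe a daily log of these exercises.

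Set any threshold for measure 3 before the data are examined. Recruitment began on 28.2.2019 under protocol version 1.0, so the change needs a dated amendment that states what had been seen by then.

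Daily step counts and weekly calls already supply measures 1 to 3, so the data cost is small. The other costs are an amendment during recruitment and, probably, a lower headline compliance figure. Steps will also give little credit for the swimming or cycling that the protocol encourages, and the report should say so.

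### Change in VO2 is defined only per kilogram of body weight, so in this single-arm pre/post comparison it mixes change in oxygen uptake with change in weight

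*Protocol article*

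**What the plan says.** The CPET row of Table 2 (Study outcomes) reads "Change in VO2 peak (ml/min/kg), change in VO2 at AT (ml/min/kg) and change in FEV1 prior and post intervention". VO2 peak and VO2 at AT are the two measures of exercise capacity, and ml/min/kg is the only unit given for either. FEV1 is not weight-indexed, but it is a spirometry measure and not a measure of exercise capacity. Body weight is not among the outcomes. The sarcopenia row lists L3 muscle area on CT, together with "change in fat composition and volume measured by CT scan and change in grip strength pre and post intervention".

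The first CPET is done during staging, before chemotherapy (Baseline measurement; Cardiopulmonary exercise testing). The second is done in the last two weeks before surgery (Completion of the exercise intervention).

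Three places bear on whether weight is stable between the two tests:

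- The Introduction reports that a "reduction in muscle mass (sarcopenia) on CT scan analysis in the interval between commencing chemotherapy and undergoing surgery has previously been observed", and reports a fall in cardiopulmonary reserve over the same interval.
- Usual clinical care during the study foresees nutritional difficulty: "Those patients that are struggling nutritionally are then reviewed by one of two specialist upper gastrointestinal dietitians". For patients who cannot take in enough, "they may have a naso-enteric feeding tube placed or a feeding jejunostomy so that they receive sufficient calories".
- The Abstract makes changing body composition a subject of study: "The secondary outcomes will evaluate changes in cardiopulmonary reserve, sarcopenia and fat composition".

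The design is single-group. The Statistical analysis section compares pre and post values by t test or Mann-Whitney test and estimates the effect with 75% confidence intervals. Weight does not enter either step.

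**The concern.** Per-kg VO2 is a ratio of oxygen uptake to body weight. Its change within a patient measures change in fitness cleanly only when weight is stable, and the article itself gives reasons to doubt that. Weight may fall through loss of muscle or poor intake, or it may be held or raised by tube feeding. There is no control group in which a common weight trend would cancel.

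At stake is the secondary aim, a preliminary look at physiological benefit meant to inform the design of a randomised trial. The Discussion hopes that the decline in fitness during chemotherapy can be prevented. On a per-kg scale, falling weight can make a decline look smaller than it is, or look like stability.

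**Working it through.** The article states no VO2 effect, SD, power or weight-change figure, and the sample size of 40 rests on guidance for pilot studies. There is therefore no figure of the plan's own to reproduce. The check uses the definition of the ratio.

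**Inputs from the article:** unit ml/min/kg (Table 2); n = 40 (Estimation of sample size); 75% confidence intervals (Statistical analysis); completion threshold 75% (Table 1).

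**Assumed inputs, not in the article:** weight at each test is the divisor, which is the ordinary meaning of the unit; weight change from a 10% loss to a 3% gain; baseline VO2 of 15 to 25 ml/min/kg; SD of change of 2 to 3 ml/min/kg.

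**Step 1: absolute VO2 unchanged.** With fractional weight loss w, the relative change in per-kg VO2 is 1/(1 − w) − 1.

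| Weight change | Change in per-kg VO2 | From 15 | From 20 | From 25 |
|---|---|---|---|---|
| 3% loss | 1/0.97 − 1 = +3.1% | +0.46 | +0.62 | +0.77 |
| 5% loss | 1/0.95 − 1 = +5.3% | +0.79 | +1.05 | +1.32 |
| 10% loss | 1/0.90 − 1 = +11.1% | +1.67 | +2.22 | +2.78 |
| 3% gain | 1/1.03 − 1 = −2.9% | −0.44 | −0.58 | −0.73 |

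Example: 80 kg at 20 ml/min/kg is 1600 ml/min. With uptake still 1600 ml/min, a weight of 76 kg gives 1600/76 = 21.05 ml/min/kg. The change in ml/min is exactly 0.

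**Step 2: absolute VO2 also falls.** With a fractional fall d in absolute VO2, the relative change is (1 − d)/(1 − w) − 1.

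| Fall in absolute VO2 | 5% weight loss | 8% weight loss | 10% weight loss |
|---|---|---|---|
| 5% | 0.0% | +3.3% | +5.6% |
| 10% | −5.3% | −2.2% | 0.0% |

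Per-kg VO2 rises only when w exceeds d. When w is below d it falls, but by less than absolute VO2 does. When the two are equal it does not move.

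**Step 3: scale against the planned interval.** The 75% half-width is 1.15 × SD/√n.

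- n = 40: 1.15 × 2/√40 = 0.36 and 1.15 × 3/√40 = 0.55 ml/min/kg.
- n = 30 (75% of 40): 0.42 and 0.63 ml/min/kg.

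A mean weight loss of 5% at unchanged absolute VO2 shifts the mean by about 1.05 ml/min/kg from a baseline of 20. Under these assumptions, that shift is larger than the half-width in every case.

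**The case against.** The strongest reply is that nothing here is contradictory or miscalculated. The unit is stated clearly, and nothing in the sample size or the success thresholds depends on VO2. The article reports loss of muscle on CT, not loss of body weight; it does not say which weight is the divisor; and the nutritional support it describes works against weight loss. Neither the size nor the net direction of the distortion can be read from the documents. The CT muscle, CT fat and grip-strength rows would also show wasting beside any per-kg rise. Finally, absolute VO2 comes from the same gas analysis and could be recovered later.

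Most of this stands and limits the point. It does not remove it. The CT and grip rows would partly reveal wasting, but they do not separate uptake from weight in the VO2 change. That absolute values are recoverable is a reason to define them now. The unit is a choice the article makes in its outcome definitions, not a detail left to a fuller document.

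Two stronger readings are tempting and are not supported:

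- A reader might infer that weight loss will show as improved fitness. That requires weight to fall proportionally more than VO2. The Introduction reports that cardiopulmonary reserve and muscle mass both fell over this interval, so the per-kg value may fall, stay flat or rise.
- A reader might infer that a distorted effect or SD will be carried into the later randomised trial. Study aims says that results will inform its design, but names no VO2 effect or SD for that purpose, and says that ChemoFit data are not intended for use in future trials.

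**Conclusion.** The point holds as a weakness in how a secondary outcome is defined. Reporting VO2 per kilogram is legitimate; the defect is that it is the only scale defined for exercise capacity in an uncontrolled comparison across a period of expected change in body composition. The distortion can run in either direction, and the documents do not establish which. The figures of 3.1, 5.3 and 11.1% are illustrations that rest on assumed weight losses of 3, 5 and 10%, unchanged absolute VO2, and weight at each test as the divisor; the ml/min/kg equivalents also need the assumed baseline. Recruitment, completion and compliance are unaffected. What is weakened is the reading of preliminary physiological benefit.

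**What to change.** In the CPET row of Table 2, define change in VO2 peak and change in VO2 at AT both in absolute terms (ml/min) and per kilogram (ml/min/kg), and add change in body weight between the two CPETs. Interpret the preliminary fitness change from the two scales together, with the weight change in view. No formal rule tying one scale to the other is needed.

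The cost is a few table rows and a recorded weight at each test. The gas analysis already planned gives ml/min before division by weight, so no extra test is required and the sample size does not change.
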